### Theoretical frameworks

The present study draws upon guidance from two frameworks: process evaluation of complex interventions: Medical Research Council (MRC) guidance (27) and the Supportive, Active, Autonomous, Fair and Enjoyable (SAAFE) principles (41).

#### Process evaluation

A comprehensive process evaluation will be conducted for the *PRO-HIIT* intervention, which will be guided by the MRC process evaluation framework (27). The framework contains three domains, including implementation (i.e., fidelity, reach, recruitment and retention, dose delivered and adaptation), mechanisms of impact (i.e., mediators, dose received, unintended consequences and response) and context (i.e., barriers, facilitators, and contamination). The MRC framework, in conjunction with insights from a recent school-based HIIT review by Liu et al. (23), will guide the adaptation of process evaluation measures tailored specifically to *PRO-HIIT*, as detailed in Table 3.

**Table 3 T3:** Medical research council definition for process evaluation and its application to the *PRO-HIIT* intervention.

Measurements	MRC definition	Apply to *PRO-HIIT*	How
Implementation: The process through which interventions are delivered, and what is delivered in practice.			
Fidelity	The consistency of what is implemented with the planned intervention.	HIIT intensity.	HR and RPE
Reach	The extent to which a target audience comes into contact with the intervention.	Schools or participants contacted.	Recruitment
Dose delivered	How much intervention is delivered.	HIIT session length, frequency and intervention duration/sessions in the protocol.	Protocol
Recruitment & retention	NG	Number of participants who are randomised and completed the intervention.	Training logbook and outcome assessment
Adaptation	Alterations made to an intervention in order to achieve better contextual fit.	Changes being made to facilitate *PRO-HIIT*.	Training logbook and teachers’ focus group
Mechanisms of impact: The intermediate mechanisms through which intervention activities produce intended (or unintended) effects.			
Mediator	Intermediate processes which explain subsequent changes in outcomes.	Mediators (e.g., sex, baseline CRF and BMI) influencing the outcome assessment.	Data analysis
Dose received	NG	HIIT sessions participants performed.	Training logbook
Unintended consequences	NG	Adverse events or other unanticipated fairs recorded.	Training logbook
Response	How participants interact with a complex intervention.	Feedbacks from participants and teachers.	Focus group and questionnaire
Context: Factors external to the intervention which may influence its implementation, or whether its mechanisms of impact act as intended.			
Barriers	Contextual factors which undermine implementation, intervention mechanisms and outcomes.	Anything restrains the implementation of *PRO-HIIT.*	Focus groups
Facilitators	Contextual factors which facilitate implementation, intervention mechanisms and outcomes.	Anything supports the implementation of *PRO-HIIT.*	Focus groups
Contamination	NG	Blinding	Blinding of research assistants; Focus groups.

MRC, medical research council; HIIT, high-intensity interval training; HR, heart rate; RPE, rating of perceived exertion; NG, not given.

It is important to highlight that while all the intervention classes will be encouraged to exercise with “all out” efforts during the HIIT sessions, the intensity will be monitored in only two randomly selected classes on one occasion per week (during one of their PE lessons) to minimise extra burden for PE teachers. The intensity in these two classes will be measured using either heart rate (HR) or rating of perceived exertion (RPE) by Polar Verity Sense and OMNI Perceived Exertion Scale for resistance exercise (42), respectively. Of note, due to resource constraints, only 10 Polar Verity Sense monitors will be utilised and rotated weekly among participants in the HR monitoring class. However, all participants will be required to report their RPE during the HIIT session once per week in the RPE monitoring class.

#### SAAFE principles

SAAFE principles offer a structured framework designed to inform the design, delivery, and evaluation of PA interventions (41). SAAFE principles provide essential guidelines and practical strategies to enable practitioners to organise their interventions in a way that not only maximises PA participation but also fosters positive affective, cognitive, motivational, and movement skill outcomes. The principles and strategies will be incorporated into the exercise design, intervention delivery and outcome assessment processes of the *PRO-HIIT* intervention (Table 4). These principles will be applied or achieved through the process of exercise design, training workshops, HIIT session delivery and outcome assessments.

**Table 4 T4:** Definition and application of SAAFE principles in the *PRO-HIIT* intervention.

Principles	Definition	Apply to *PRO-HIIT*	How
Supportive	Intervention is designed to facilitate a supportive environment	Encourage praise of students’ effort and improvement during HIIT sessions and outcome evaluation process.	Researchers and teachers’ training workshop.
		Encourage mutual support when performing HIIT and outcome assessments.	Students’ training workshop.
		Demonstrate empathy toward students when they feel frustrated or challenged.	Researchers and teachers’ training workshop.
Active	Sessions are highly active	Sessions are designed without any instruction time.	Exercise design.
		Exercises are performed at high intensity.	Encourage exercise with “all out” efforts.
Autonomous	Sessions involve elements of choice	Right to play any music they like.	Students’ training workshop.
		Self-organisation.	Peer coaches to lead the HIIT sessions.
		Right to choose exercises from an exercise pool (final 3 weeks).	Every Friday prior to the week the exercise will be performed.
		Perform the missed HIIT sessions themselves during breaks.	Under the supervision of peer-coaches and record on training logbook.
		Minimize controlling language.	Researchers and teachers’ training workshop.
Fair	Intervention provides all students with opportunities to experience success	Encourage self-comparison rather than peer-comparison.	Students’ training workshop.
		Provide personalised care for individuals with special needs (e.g., participants with lower fitness levels).	Simplify exercises or lower exercise intensity (PE teacher’ discretion).
Enjoyable	Intervention is designed to be enjoyable and engaging for all students	Provide different HIIT workouts.	From existing literature.
		Provide challenging HIIT sessions.	Progressively increase the exercise duration and intervals within and across sessions.
		Play music while exercising.	Peer-coaches.

HIIT, high-intensity interval training; PE, physical education.

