The HIIT sessions consist of body-weight resistance exercises (e.g., high knees, jumping jacks, burpees), selected based on relevant literature (33, 40). The session length will be progressively extended from 6 to 10 min over the 12 weeks, accounting for fitness adaptations. Within each session, the work-to-rest ratio will increase from 10 s: 20 s, to 15 s: 15 s, until 20 s: 10 s as the exercise progresses. Furthermore, participants will perform one exercise (e.g., jumping jacks) twice in a minute to avoid monotony while preventing frequent exercise changes, thereby 6, 8 and 10 different exercises will be completed as the intervention duration increases. Moreover, flexibility will be allowed for each HIIT session, enabling adaptations whenever necessary (e.g., higher/lower exercise intensity). The adaptations made will be recorded on the training logbook. The details regarding the exercises are presented in Table 1.

To facilitate the implementation process, several strategies will be employed, including:
(1)training workshops for participants, peer-coaches, teachers and research staff (Table 2);(2)providing participants with opportunities to choose music and exercises (from an exercise pool over the final 3 weeks of the intervention);(3)the opportunity to win a prize upon completion of the intervention for all participants.

**Table 2 T2:** Details of training workshops for participants, peer-coaches, teachers and research staff.

Subjects	Timing	Content
Participants (CON)	Two PE lessons (40 min)	(1) Introduction of the programme; (2) outcome measurements; (3) familiarisation of executive function tasks; (4) maintain daily life.
Participants (INT)	Two PE lessons (80 min)	(1) Introduction of the programme; (2) familiarisation of equipment (e.g., HR monitor), executive function tasks and HIIT exercises; (3) outcome measurements.
Peer-coaches	One PE lessons (40 min)	(1) HIIT performing and leading; (2) HIIT rescheduling and regulation.
PE teachers	60 min	(1) Introduction of the programme; (2) familiarisation of equipment (e.g., HR monitor); (3) HIIT exercises; (4) training logbook; (5) intervention delivery.
Research staff	60 min	(1) Outcome measurements; (2) data collection principles (e.g., SAAFE).

CON, control group; INT, intervention group; PE, physical education; HR, heart rate; HIIT, high-intensity interval training; SAAFE, the supportive, active, autonomous, fair, enjoyable principles.

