### Outcome measurements

Outcome measurements will be conducted in the school premises by trained research assistants who will remain blinded to group allocation throughout all assessment time-points. All measurements will be introduced and explained during the training workshop and will be described again prior to the commencement of the measurements to ensure clarity. The measurements will be conducted during their regular PE lessons. Details of the outcome measures are summarised in Table 5.

**Table 5 T5:** How, when and where the outcome variables will be measured.

Outcomes	Tools	Timing	How and where (all participants, measured at class level)
Physical activity	GENEActiv	One week before and after intervention, first and last week of intervention.	A subsample of 60 participants (30 in each group, 30 males) will be randomly selected to wear the GENEActive accelerometer for 14 days consecutively for twice, covering the total 4 weeks.
Cardiorespiratory fitness	20 m shuttle run	T1, T2, T3	Multiple measurement stations will be held, and participants will be split into groups to ensure efficient measurements. Two physical education lessons are estimated to be sufficient. All these measurements will be conducted in sports hall.
Body composition	TANITA	T1, T2, T3	
Muscular strength	Handgrip, standing long jump	T1, T2, T3	
Bone health	GE Achilles	T1, T2, T3	
Executive function	Flanker tasks, visual 2-back tasks, colour-shape switch tasks	T1, T2, T3	Perform the executive function tasks online in a school computer room in one physical education lesson (40 min).
Wellbeing	SDQ	T1, T2, T3	Finish together using one physical education lesson (40 min) in a school computer room with the instruction of research staff.
Enjoyment	PACES	T1, T2, T3	
Motivation	BREQ-2	T1, T2, T3	
Affect	PANAS-SF	T1, T2, T3	
Self-efficacy	PPAS	T1, T2, T3	
Academic performance	End-of-term academic examinations	By the end of term 1 and T2	Obtained directly from head teacher.

SDQ, strength and difficulty questionnaire; PACES, physical activity enjoyment scale; BREQ-2, exercise regulations questionnaire; PANAS-SF, positive and negative affect schedule short form; PPAS, perceived physical ability scale; T1, pre-intervention; T2, immediately post-intervention; T3, 2-month follow-up.

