#### Primary outcome

##### Cardiorespiratory fitness

CRF will be assessed using the 20 m-SRT, a well-established field test for evaluating CRF (43). The 20 m-SRT requires participants to run back and forth between two lines positioned 20 meters apart. Participants must reach the other end before a designated beep sounds. The beep is set to allow the participants to start at 8.5 km/h with increases in speed of 0.5 km/h denoted by a triple beep. The test concludes if a participant fails to complete two consecutive shuttles or volitionally discontinues. Performance on the 20 m-SRT will be reported as number of laps completed. The test will be administered by the same group of research assistants at the same location, time of the day and with consistent levels of verbal encouragement across all measurement timepoints to avoid biased results.

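### Table 4 carries praise of improvement and peer support into the outcome assessments without exempting the effort-dependent 20 m shuttle run, in unreconciled tension with that test's rule of consistent encouragement

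*Protocol article*

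**What the plan says.** **SAAFE principles (text and Table 4).** The principles are to be "incorporated into the exercise design, intervention delivery and outcome assessment processes", so they are meant to reach beyond the exercise sessions. In the Supportive rows, a workshop for researchers and teachers covers praise of pupils' "effort and improvement during HIIT sessions and outcome evaluation process". The pupils' workshop has its own row: "Encourage mutual support when performing HIIT and outcome assessments".

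**Intervention delivery and exercise design (Table 2).** The research staff workshop names SAAFE as an example of the principles for collecting data.

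**Primary outcome, Cardiorespiratory fitness.** The test ends when a pupil "fails to complete two consecutive shuttles or volitionally discontinues", and the result is the number of laps. The same group of assistants runs it "with consistent levels of verbal encouragement across all measurement timepoints to avoid biased results".

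**Outcome measurements (text and Table 5).** Trained research assistants, blinded to allocation at every timepoint, take the measurements in ordinary PE lessons, class by class.

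The article does not say whether the shuttle run is exempt from the Supportive rows, or how praise and peer support are to be kept alike across visits and arms.

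**The concern.** A lap count from a test that the pupil may end at will reflects both fitness and willingness to continue. The protocol recognises this: it gives avoidance of bias as the reason for holding encouragement steady. Table 4 then adds two further sources of encouragement in the same assessments, and neither is governed by that rule. Praise for improvement is tied to the visit, because a first shuttle run has no earlier result to improve on. Support from classmates and teachers is not something the assistants control.

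Two kinds of estimate are at stake. One is change over time, which matters for the second aim (change across the summer break) and for the time effects in the linear mixed model. The other is the group-by-time comparison of the primary outcome, but only if encouragement comes to differ between the arms.

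**Working it through.** **1. The plan's own figure.** Inputs from Sample size estimation: d = 0.31, 80% power, alpha 0.05, two groups. Two-sided, n per group = 2 × (1.960 + 0.842)² / 0.31² = 15.70 / 0.0961 ≈ 163.4, or 164 by the normal approximation. The t-test solution is 164.3, which rounds up to the stated 165. The figure reproduces, and nothing in this point changes it.

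**2. The rules side by side.**

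| Source of encouragement | Governing text | Can it be alike at T1, T2 and T3? | Covered by assistant blinding? |
|---|---|---|---|
| Assistants, praise of effort | Table 4 and Cardiorespiratory fitness | Yes | Yes |
| Assistants, praise of improvement on the shuttle run | Table 4 and Cardiorespiratory fitness | No: there is no earlier result at T1 | Yes |
| Classmates | Table 4 only | Not stated | No |
| PE teachers, if present | Table 4 only | Not stated | No: they supervise the HIIT sessions and so know the allocation |

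**3. What each kind of inequality does.** Let encouragement add p1, p2 and p3 laps at T1, T2 and T3.

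- *Same in both arms.* The change from T1 to T2 is shifted by p2 − p1, and the change from T2 to T3 by p3 − p2. Praise of improvement makes p1 the odd one out. It also makes p3 differ from p2 if pupils have less improvement to be praised for after the summer. In the group-by-time contrast the shifts cancel.
- *Different between arms.* The contrast at T2 is shifted by p2(intervention) − p2(control), and likewise at T3. Allocation follows baseline assessment (Recruitment and allocation), so knowledge of the allocation can affect only T2 and T3. When a class is tested together, the classmates giving support all belong to one arm, so each arm has its own peer environment.

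**4. Illustration of scale (assumed shifts).** The documents give no encouragement effect. If the cited 9-lap gain divided by d is taken as the SD, then SD = 9 / 0.31 ≈ 29 laps, or 9 / 0.69 ≈ 13 laps. With 165 per group and clustering ignored, SE = SD × √(2/165) = 0.110 × SD, about 3.2 or 1.4 laps. With no true effect and an assumed shift b between arms, the two-sided rejection rate is Φ(−1.96 + b/SE) + Φ(−1.96 − b/SE).

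| Assumed shift b | Share of 9 laps | Error rate, SD 29 | Error rate, SD 13 |
|---|---|---|---|
| 0 | 0% | 5% | 5% |
| 1 lap | 11% | 6% | 11% |
| 2 laps | 22% | 10% | 29% |
| 3 laps | 33% | 16% | 55% |

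Allowing for clustering would widen the SE and lower these rates. The table shows only that a shift of a few laps would not be negligible. It is not evidence that such a shift will occur.

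**The case against.** The strongest reply is that the two sections can be obeyed together. The shuttle run section permits encouragement, asks only that its level be consistent, and is the specific rule, whereas Table 4 states general principles for all assessments. A reader might infer an outright contradiction with a fixed encouragement script. The text does not support that, because there is no script, and equal praise of effort at each visit would satisfy both. What remains is praise of improvement on this test, which cannot be equal at T1, and peer support, which the specific rule does not mention.

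A reader might also infer that the primary comparison is biased towards the intervention. The documents do not establish this:

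- Nothing in Table 4 limits praise or support at assessments to one arm, and Table 2 lists the outcome measurements in both arms' pupil workshops.
- The assistants are blinded, and the same group is used throughout.
- Randomisation is stratified by PE teacher, which limits confounding of teacher style with arm, although it does not blind the teacher.
- The article does not say that teachers take part in testing. Table 2 names SAAFE for research staff only, and the Table 4 praise row also covers HIIT sessions, where teachers plainly act.
- Intervention classes will reach T2 used to maximal effort led by their peers, but that follows from an exercise intervention that cannot be blinded. Editing Table 4 would not alter it.

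Improvement can also be praised within one visit, for example over the three standing long jump attempts, and no text says that assistants hold or announce earlier lap scores. These points stand. They reduce the point from a shown bias to an avoidable risk.

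Finally, a detailed testing script belongs in a manual that an article may omit. That is fair for the script. It does not answer the point that Table 4, as published, extends these practices to the assessments with no exemption.

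**Conclusion.** The point holds as an unreconciled tension between Table 4 and the shuttle run section. Followed literally, praise of improvement makes encouragement on the primary test differ between T1 and the later visits, which can distort estimates of change over time even when both arms are treated alike. Unequal support between arms, from classmates or from teachers who happen to be present, is plausible because testing and randomisation share the class as their unit. It is not demonstrated.

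The documents give no size. A reader might infer that 20% to 40% of the expected effect is at risk by assuming 1-minute stages (8.5 km/h = 141.7 m/min ≈ 7.1 laps), and that pupils stop a quarter to half a stage later (1.8 to 3.5 laps, or 20% to 39% of 9). Neither the stage length nor the delay is in the protocol, so that range should not be read as an estimate. The error rates shown in the check depend equally on assumed shifts. The wording should be changed because the outcome is primary and the correction is cheap. The sample size is unaffected.

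**What to change.** 1. In Table 4, limit the two Supportive rows on praise and on mutual support to HIIT sessions. Alternatively, keep them and exempt the effort-dependent tests: 20 m shuttle run, standing long jump and handgrip.
2. In the Cardiorespiratory fitness section, with a cross-reference for the two strength tests, state that encouragement comes only from the blinded research assistants, in the same standard form in both arms and at T1, T2 and T3. State also that there is no comment on improvement or earlier scores until after T3.
3. Bring the research staff workshop in Table 2 into line, so that SAAFE is not taught as applying to these tests without that limit.

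The cost is a few lines of text, a small change to the workshops and a short standard wording for the assistants. The downside is a slightly less supportive testing session and possibly slightly lower lap counts in both arms.

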### Outcome measurements

Outcome measurements will be conducted in the school premises by trained research assistants who will remain blinded to group allocation throughout all assessment time-points. All measurements will be introduced and explained during the training workshop and will be described again prior to the commencement of the measurements to ensure clarity. The measurements will be conducted during their regular PE lessons. Details of the outcome measures are summarised in Table 5.

**Table 5 T5:** How, when and where the outcome variables will be measured.

Outcomes	Tools	Timing	How and where (all participants, measured at class level)
Physical activity	GENEActiv	One week before and after intervention, first and last week of intervention.	A subsample of 60 participants (30 in each group, 30 males) will be randomly selected to wear the GENEActive accelerometer for 14 days consecutively for twice, covering the total 4 weeks.
Cardiorespiratory fitness	20 m shuttle run	T1, T2, T3	Multiple measurement stations will be held, and participants will be split into groups to ensure efficient measurements. Two physical education lessons are estimated to be sufficient. All these measurements will be conducted in sports hall.
Body composition	TANITA	T1, T2, T3	
Muscular strength	Handgrip, standing long jump	T1, T2, T3	
Bone health	GE Achilles	T1, T2, T3	
Executive function	Flanker tasks, visual 2-back tasks, colour-shape switch tasks	T1, T2, T3	Perform the executive function tasks online in a school computer room in one physical education lesson (40 min).
Wellbeing	SDQ	T1, T2, T3	Finish together using one physical education lesson (40 min) in a school computer room with the instruction of research staff.
Enjoyment	PACES	T1, T2, T3	
Motivation	BREQ-2	T1, T2, T3	
Affect	PANAS-SF	T1, T2, T3	
Self-efficacy	PPAS	T1, T2, T3	
Academic performance	End-of-term academic examinations	By the end of term 1 and T2	Obtained directly from head teacher.

SDQ, strength and difficulty questionnaire; PACES, physical activity enjoyment scale; BREQ-2, exercise regulations questionnaire; PANAS-SF, positive and negative affect schedule short form; PPAS, perceived physical ability scale; T1, pre-intervention; T2, immediately post-intervention; T3, 2-month follow-up.

#### Primary outcome

##### Cardiorespiratory fitness

CRF will be assessed using the 20 m-SRT, a well-established field test for evaluating CRF (43). The 20 m-SRT requires participants to run back and forth between two lines positioned 20 meters apart. Participants must reach the other end before a designated beep sounds. The beep is set to allow the participants to start at 8.5 km/h with increases in speed of 0.5 km/h denoted by a triple beep. The test concludes if a participant fails to complete two consecutive shuttles or volitionally discontinues. Performance on the 20 m-SRT will be reported as number of laps completed. The test will be administered by the same group of research assistants at the same location, time of the day and with consistent levels of verbal encouragement across all measurement timepoints to avoid biased results.

